### Confidentiality

All forms with participant information for this study are stored in a locked filing cabinet in the PI’s office with access limited to specified members of the research team. Upon entry to the study, participants are given a number and this number is then used on all documents, apart from the consent form and within the database. The study data are stored in a password protected database with access limited to the PI, the statistician and members of the research team tasked with data entry and verification.

#### Testing sessions and timeline

Participants are asked to attend a total of four testing sessions (see Fig. 1), all conducted at the academic institution’s Human Performance Laboratory. During the first visit, anthropometric variables of, height (Detecto, Webb City, Missouri), weight and body composition via bioelectrical impedance (BC-418,Tanita,Tokyo, Japan) are assessed along with the determination of peak oxygen uptake (VO_2peak_) using a computerized metabolic cart (MAX-II, AEI Technologies, Pittsburg, PA), that is calibrated according to manufacturer’s specifications. The cardiopulmonary exercise test is performed on a motor driven treadmill with a Q-stress system (Welch Allyn, Skaneateles Falls, NY) using the Modified Bruce protocol. Resting cardiovascular (CV) variables (i.e., central and peripheral blood pressure, pulse wave velocity and pulse wave analysis) are assessed using applanation tonometry (SphygmoCor Excel, AtCor Medical Inc., Itasca, IL) after a 10-min rest period in the supine posture. One week later, patients return to the Human Performance Laboratory for their second baseline visit following at least an 8-h fast. On arrival, a blood sample is taken, and processed by spinning in a refrigerated centrifuge (4 °C, and spun at 3000 rpms for 15 min). The plasma is then removed and placed in 10 storage tubes and stored in a − 80° freezer for later analysis. Prior to visit 2, participants collect a stool sample at home and complete a 3-day food record documenting the brand, portion size, and preparation methods of all foods and beverages consumed. Both the stool sample and the food records are brought to the lab for visit 2. Following baseline testing, subjects are assigned randomly to one of 4 groups ensuring equal number of subjects in each group: Group A receives the prebiotic supplement with usual care but no prescribed exercise, Group B receives the prebiotic supplement and performs supervised aerobic exercise training at a moderate intensity for 16 weeks, Group C receives the placebo (cornstarch) supplement along with 16 weeks of moderate intensity aerobic exercise training, while group D receives the usual care and the placebo but no supervised exercise training. The randomization was performed by the study statistician prior to the start of the study.

**Fig. 1 Fig1:**
[figure not shown]
The schedule of enrollment, interventions, and assessments.*

#### Follow-up testing

All of the aforementioned variables (except the stool sample, and the VO_2peak_ test) are reassessed after 8 and 16 weeks of participation in the study. The final stool sample and the post-training VO_2peak_ test are done after week 16. All post-tests are performed at least 48- h following the completion of the final training session to avoid the residual effect of the final training session.

### Analysis of biomarkers

#### Analysis of inflammatory and oxidative stress markers

Venous blood samples are being collected at BL, Wk8 and Wk16. A 21- or 23-gauge needle (BD Vacutainer® Safety Lok and Vacutainer® one-use holder, Becton, Dickinson and Company, Franklin Lakes, NJ) is used to collect two, 10 mL of blood at each of the time point and placed into an appropriate collection tubes (EDTA Monoject Vacutainer, Coviden, Mansfield, MA) by trained personnel. Plasma is obtained from the EDTA tubes through centrifugation immediately after collection at 1500 g for 15 min at 4 °C. Plasma samples are being stored at − 80 °C until ELISA assays are conducted for the analyte panel, including: CRP, malondialdyhide (MDA), and nitrate/nitrite (Cayman Chemical, Ann Arbor, MI), Cytokine panel (TNFα, IL-6, IL-10), Enothelin-1, (Millipore, Burlington, MA), MCP-1 (Eagle Biosciences, Amherst, NH), and 8-isoprostane (Cell Biolabs, San Diego, CA). All samples will be measured in duplicate, in accordance with manufacturers’ recommended protocol and be within acceptable variance and above sensitivity provided from the manufacturer.

#### Analysis of uremic toxins

The concentration of IS and PCS in the plasma is measured by reverse-phase HPLC. In brief, 0.24 M sodium octanoate is added in plasma as a competitor to replace non-covalent binding of *p*-cresyl sulfate and indoxyl sulfate to albumin. After 5 min incubating at room temperature, the plasma is deproteinized by adding 4 parts of cold acetone to 1 part of plasma. The mixture is then centrifuged at 3000×*g* for 20 min at 4 °C and the supernatant is measured by HPLC (Waters 1525 binary HPLC system coupled with 2475 fluorescence detector) [20].

#### Analysis of stool samples

Stool will be used for microbial assessment by 16 s RNA sequencing (MiSeq platform, 2 × 300 bp). The pipelines of QIIME2 with DADA2 will be used to perform demultiplexing sequences, quality control, feature table construction and taxonomy assignment [21]. Taxonomic assignment (from kingdom to genus level) of the representative sequences of each sample will be performed using the Silva 132 pre-trained Naive Bayes classifier and the q2-feature-classifier plugin in the QIIME2 pipeline. Alpha-diversity will be calculated by observed species, Chao1, and Shannon indices using QIIME2. To compare microbial profiles between samples, weighted (quantitative) and unweighted (qualitative) variants of UniFrac and Bray-Curtis will be measured. Principal coordinate analysis (PCoA) will be applied on the resulting distance matrices to generate two-dimensional plots. Permutational multivariate analysis of variance (PERMANOVA) will be used to statistically test for significant differences of the microbial profile between groups. Hierarchical clustering analysis will be performed to show a visual interpretation heatmap of the similarity of microbial taxa and function gene among groups. In terms of downstream microbiome analysis, centered Log Ratio Transformation (CLR) will be applied to transform the microbiome composition. The longitudinal model (MetaLonDA) [22] and the generalized estimating equation (GEE) model [23] will be performed to compare the dynamics of microbial composition over time between groups. Within each arm, the repeated ANOVA with permutation test will be used to analyze microbial composition.

### Interventions

#### Nutrition protocol

Participants are randomized to receive a supplement of either resistant starch (intervention) or waxy cornstarch (control). The study dietitian (DC) is the only “unblinded” member of the research team, and is responsible for providing the correct supplement to participants, without revealing the randomization scheme to other team members or participants. At the completion of the study, DC reveals the contents of the supplement to the participant. The resistant starch is composed of 40% digestible starch and 60% resistant starch and is provided as Hi-Maize® 260 resistant starch (Hi-Maize 260, Ingredion, Bridgewater, NJ). The control is Amioca® corn starch (AMIOCA, Ingredion, Bridgewater, NJ), is nearly completely digestible. For week 1, the dose of supplements is 15 g/day. The dose is then increased to 33 g/day for weeks 2–16. Participants are instructed to blend their supplement into commonly consumed foods/beverages such as yogurt, soups, oatmeal, coffee, or juice. This daily dose was selected to provide a minimum of 30 g resistant starch/day as previously reported by Sirich et al. [9], and allow for the 10% variability in the sachet weight as determined by the commercial packing company. Sirich et al. [9] utilized a similar protocol with good gastrointestinal tolerance. Participants are provided with dosing suggestions and recipes to promote good compliance. Supplements are provided to participants as daily doses in sachets labeled as either “Supplement 1” or “Supplement 2”. Participants are issued half of their daily doses of supplement at visit 2, and the remaining daily doses of supplement are provided at visit 3. Participants are instructed to return any unused supplement at the completion of the study. A research assistant contacts the subjects biweekly during the study to determine if the subject had experienced any complications with consuming the supplement and to encourage compliance. Three-day food records are administered at baseline, and week 16 and entered into Food Processor software (ESHA) for nutrient analysis -to assess between-group differences in dietary intake of nutrients which may impact upon renal function (i.e. protein, potassium, phosphorus).

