### Data auditing

Prior to performing the final study analyses, data will be checked by the statistician who will be assisted by research assistants in this process. These individuals will be blinded to the group assignment of the participants.

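### With only two sachet labels for the whole trial, disclosing contents at what reads as each participant's own finish could unblind those still to be enrolled or treated; disclosure should wait until database lock

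*Protocol article*

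**What the plan says.** All on the point comes from the protocol article.

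- **Labels.** Nutrition protocol: "Supplements are provided to participants as daily doses in sachets labeled as either “Supplement 1” or “Supplement 2". These are two codes for the whole trial, one per product.
- **Disclosure.** Same section: at the completion of the study the dietitian "reveals the contents of the supplement to the participant".
- **Same phrase, used again.** Same section: "Participants are instructed to return any unused supplement at the completion of the study".
- **Who is unblinded.** Same section: the dietitian "is the only “unblinded” member of the research team".
- **Timing.** Inclusion criteria: 60 patients in a study run over 3 years. Recruitment: patients are approached individually at their clinic appointments. Each person has 16 weeks of supplement.
- **Statistician.** Testing sessions and timeline: "The randomization was performed by the study statistician prior to the start of the study". Data auditing, on the statistician and research assistants who check the data: "These individuals will be blinded to the group assignment of the participants".
- **Laboratories.** Outcomes: the laboratories assaying the biochemical markers are blinded to group.
- **Current analysis.** Update: exercise has been removed and comparisons involving it are exploratory. Prebiotic against placebo over three time points is the remaining planned comparison.

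**The concern.** A two-code scheme is only as strong as its weakest disclosure. Whoever learns what one label contains also knows the other by elimination, and the labels are the same for everyone. If early completers are told their product while others are still being enrolled or treated, the key to the trial is in circulation, and the plan itself has released it.

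What is at stake is the supplement comparison, the one comparison that the Update does not reduce to exploratory. Participants who believe they know their product may change how faithfully they take it, what they eat, or whether they stay. Supplement use of at least 70% also helps to define the per-protocol set, and missing data from dropouts are to be multiply imputed, so both analyses would inherit any such behaviour. Staff who know the code could be influenced when measuring blood pressure and pulse wave velocity.

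**Working it through.** The plan gives no figure on this point, so there is none to reproduce. The check compares the passages and then does an illustrative accrual calculation.

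**1. When is the disclosure?** The disclosure sentence and the sachet-return sentence stand in the same section and share the same time phrase. Returning unused sachets makes sense only at a person's own last visit. The disclosure is also written in the present tense and to a single participant. Both features favour disclosure at each person's own finish. Nothing in the text rules out the end of the whole trial.

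**2. What does one disclosure reveal?** There are two products and two fixed labels. Knowing the contents of one label gives the contents of the other. The information applies to all 60 participants, but it decodes a given person only for someone who also knows that person's label. Each participant sees their own.

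**3. How many could be exposed?** Inputs:

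- One week from visit 1 to visit 2 (Testing sessions and timeline) plus 16 weeks of supplement, so the first participant finishes at about week 1 + 16 = 17.
- Total duration *T*: 156 weeks for the stated 3 years, and 104 weeks as an assumed shorter case.
- Uniform accrual over *T* − 17 weeks (assumption).

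Share not yet enrolled at first completion = 1 − 17/(*T* − 17):

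| *T* (weeks) | Accrual (weeks) | Share not yet enrolled |
|---|---|---|
| 104 | 87 | 1 − 17/87 = 0.80 |
| 130 | 113 | 1 − 17/113 = 0.85 |
| 156 | 139 | 1 − 17/139 = 0.88 |

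Counting the first participant as enrolled at week 0 and spreading the other 59, the number enrolled at week 17 is 1 + 59 × 17/(*T* − 17). That gives 12.5 for 104 weeks and 8.2 for 156 weeks, leaving 47.5 to 51.8 of 60 (79% to 86%) not yet enrolled. At that moment up to 59 have not finished.

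**4. Which outcomes are open to influence?** Blinded laboratories protect the reading of the biochemical primary outcomes. Blood pressure and pulse wave velocity are secondary and measured at study visits. Adherence, diet and retention can reach any outcome, but only indirectly, and the documents give no basis for sizing that effect.

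**The case against.** **The phrase may mean the end of the trial.** If so, the scheduled disclosure does no harm. This stands as a possibility, and the section does say that the dietitian must not reveal the scheme to participants or colleagues. It is why the point is put as the likelier reading. It does not remove the need to say which is meant.

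**A leak needs a chain of events.** A finished participant must remember the label, learn the contents and tell someone for whom that matters. The documents report no such event. The Update also reduces contact between participants: recruitment is remote, shared exercise sessions have gone, and dietary counselling is by telephone. This stands. In the other direction, the Update has the principal investigator telephone participants before each session and meet them at the visit, so a remark to one person could affect later visits.

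**The main outcomes are protected.** This largely stands for the reading of the assays. It does not extend to diet, adherence or dropout.

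**The exposure figure proves little.** It rests on uniform accrual, which the COVID-19 shutdown makes doubtful. A reader might take 80% to 88% as the share unblinded. It is only the share enrolled after a first possible disclosure.

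**The statistician.** A reader might infer a contradiction, since the statistician performed the randomization, is called blind when checking data, and the dietitian is said to be the only unblinded member. The documents do not establish that. All three statements are true together if the list was generated in masked codes and the dietitian held the key. The article does not say so, but a condensed article may leave that detail to the full protocol.

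**Conclusion.** The concern holds as a design weakness with a probable, not certain, trigger. Two shared labels are stated outright. Disclosure at each participant's own finish is the likelier reading of the Nutrition protocol section. On that reading, with staggered enrolment, an early disclosure could decode the allocation of most of those who follow, if it is passed on. Roughly 80% to 88% would be enrolled after the first possible disclosure, assuming uniform accrual in a study of 2 to 3 years. This shows how long the exposure lasts and says nothing about the size of any bias.

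The documents do not show that anyone has been unblinded or that the biochemical results are compromised. Nor do they show that the statistician's blinding has failed. The last is a matter of clarification only.

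**What to change.** 1. In the Nutrition protocol section, state that contents are disclosed to any participant only after the last participant's final visit and database lock.
2. Where stock allows, label the remaining sachets with participant-specific codes. This matters most if any disclosure has already been made, because deferral cannot recall it. If no disclosure has been made, deferral alone closes the scheduled route.
3. As a clarification, if this is what was done, state that the statistician worked with masked codes while the dietitian held the key, so that Testing sessions and timeline, Nutrition protocol and Data auditing read consistently.

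The first and third changes need only a sentence each. The cost is that early completers wait longer to learn which supplement they took. The second adds some relabelling of sachets that a commercial company has already packed.

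### Read as product weight, 33 g/day of a 60% resistant-starch product holds about 20 g of resistant starch, which does not fit the stated minimum of 30 g; the figures must be reconciled

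*Protocol article*

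**What the plan says.** All the relevant figures stand in one paragraph of the protocol article, under Interventions, Nutrition protocol.

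- Composition of the active product: "The resistant starch is composed of 40% digestible starch and 60% resistant starch and is provided as Hi-Maize® 260 resistant starch".
- Amount in the first week: "For week 1, the dose of supplements is 15 g/day".
- Amount afterwards: "The dose is then increased to 33 g/day for weeks 2–16".
- Reason for the amount: "This daily dose was selected to provide a minimum of 30 g resistant starch/day", with reference to an earlier prebiotic study (reference 9), and also to "allow for the 10% variability in the sachet weight as determined by the commercial packing company".
- Form of supply: "Supplements are provided to participants as daily doses in sachets labeled as either “Supplement 1” or “Supplement 2".

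The same gram amounts apply to both arms. The control is a waxy cornstarch described as almost wholly digestible. No other section gives a different composition or a sachet weight, or says that 33 g is a quantity of resistant starch rather than of product.

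**The concern.** The paragraph gives an amount, a composition and a resulting content. The first two determine the third, and on the plain reading the result is not the one stated.

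This matters because the quantity of active ingredient defines the intervention. The Update section removes the exercise component and makes the exercise comparison exploratory, so supplement against placebo is now the main comparison. A reader who takes the rationale at face value would attach the result, positive or null, to at least 30 g of resistant starch a day. On the paragraph's own composition, that may be about half as much again as participants were supplied (30 / 19.8 = 1.52). Anyone replicating or pooling the trial would carry the same figure forward. The claim that the amount matches an earlier protocol also depends on which quantity the 30 g denotes.

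**Working it through.** **Inputs**, all from the Nutrition protocol section: resistant fraction 0.60; amount 15 g/day in week 1 and 33 g/day in weeks 2 to 16; stated minimum 30 g/day of resistant starch; sachet variability 10%, taken here as plus or minus 10%.

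**1. Reproducing the stated figure.** It comes out only when the composition is left aside:
- 30 × 1.1 = 33.0 g, and 33 / 1.1 = 30.0 g.

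This suggests that 33 g is 30 g plus a 10% packing margin, with 30 g being a weight of product. That origin is an inference; the article does not set it out.

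**2. Applying the stated composition.** Resistant starch = product weight × 0.60.
- Nominal: 33 × 0.60 = 19.8 g/day.
- Sachet 10% light: 33 × 0.90 × 0.60 = 17.8 g/day.
- Sachet 10% heavy: 33 × 1.10 × 0.60 = 21.8 g/day.
- Week 1: 15 × 0.60 = 9.0 g/day.

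**3. Gap from the stated minimum, weeks 2 to 16.**
- 30 − 19.8 = 10.2 g/day, and 10.2 / 30 = 34%.
- Even the heavy sachet is 30 − 21.8 = 8.2 g/day short, so sachet variability cannot account for the gap.

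**4. What would have to be true for the statements to agree.**
- With 33 g as product weight, the resistant fraction would have to be 30 / 33 = 91%, against the stated 60%.
- With 33 g as resistant-starch content, the sachet would weigh 33 / 0.60 = 55 g. The article does not say this.

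**5. Which reading the text favours.** Three features point to product weight. The gram amount is given for the supplements of both arms, and a digestible control cannot contain 33 g of resistant starch. The supplement is supplied as daily sachets. The 10% allowance is tied to sachet weight. The paragraph also uses the term resistant starch both for the commercial product and for the 60% component of it, which would explain how a product weight came to be labelled as content.

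**The case against.** The strongest reply is that the article never says whether 33 g is product or content, so product weight remains an inference. If 33 g were resistant-starch content, the figures would be compatible. A second reply is that little depends on the label: randomisation, blinding, the control and the analysis concern the supplement as supplied, and none of them uses the 30 g figure. Both replies stand in part. The first makes the 19.8 g figure conditional, but it does not help the text as written, which leaves a reader unable to tell what was given. The second limits the harm to the description of the exposure.

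Some stronger readings are tempting, and the documents do not support them.

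- *The trial will report an exposure that it does not deliver.* This is a forecast. It needs 33 g to be product weight and the 30 g wording to be carried into the results.
- *Participants receive two-thirds of what the earlier study gave.* The documents do not show whether that study's figure was product or content. If it was product weight of a similar starch, the amounts could be comparable and only the label wrong.
- *The sample size is undermined.* The Sample size estimates section takes its numerical range, d of 0.40 to 0.77, from an exercise study. It cites the prebiotic study only for effects of similar magnitude and then plans on a generic medium effect. No input is tied to 30 g/day.
- *The tolerance evidence no longer applies.* If less resistant starch is supplied than in the earlier protocol, evidence of good tolerance applies at least as well.

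A sachet 10% light holds 33 × 0.90 = 29.7 g of product. The 0.3 g difference from 30 g depends on how the margin is applied and is not pressed here.

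**Conclusion.** The paragraph is inconsistent as written and needs correction. Taking 33 g as product weight and the 60% composition as accurate, the weeks 2 to 16 supplement contains 19.8 g/day of resistant starch (17.8 to 21.8 g), 34% below the stated minimum at the nominal weight. Nothing elsewhere in the article resolves this.

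The randomised comparison is unaffected. What is at risk is the statement of the exposure to which the result applies, and the claimed match with the cited protocol. A reader might infer that about 20 g is the true figure and 30 g the mistake. The documents do not settle that: the error could lie in the composition, the gram amount, the stated minimum or the unit attached to any of them.

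**What to change.** Check the composition, the gram amount and the stated minimum against the product specification and the packing company's sachet specification. Label every gram figure, including the week 1 amount, as product weight or resistant-starch content, and give the resistant starch per sachet with its tolerance. Then make the exposure statement consistent with the outcome. Restate the comparison with the cited protocol in the same unit, and use the same wording in the trial report. No dose is proposed; which figure stands is for the investigators.

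The cost is a records check and one corrected paragraph. The design, the randomisation and the analysis need no change on this account. The stated exposure may turn out lower than the article now claims.
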